## Results

### Baseline Characteristics

A total of 13,391 employees were eligible to enroll in the UMass Fitbit Care Study and received an email or home mailer about participating in the study. Of those invited, 758 completed consent to participate in less than 24 hours and scheduled an appointment for initial biometric screening. The follow-up rate was 75.7%, with 603 individuals attending the biometric screening and getting randomized to the intervention (n=300, 49.8%) or control group (n=303, 50.2%). Baseline characteristics of these 2 groups are provided in Table 2, and no systematic differences were observed between the 2 groups. On average, participants were 46.7 (SD 11.2) years of age. The majority of the participants were female (80.3%, n=484), White (85.4%, n=504), and non-Hispanic (90.7%, n=547). More than half (74.8%, n=440) of the participants had a baseline BMI that classified them as overweight or obese.

**Table 2 table2:** Baseline participant characteristics.

Characteristics		Intervention (n=300)	Control (n=303)	*P* value	
**Age (years), mean (SD)**		46.3 (11.0)	47.2 (11.4)	.34	
**Sex, n (%)**					.50
	Female	241 (80.3)	243 (80.2)		
**Race (intervention: n=295; control: n=295), n (%)**					.80
	White	254 (86.1)	250 (84.8)		
	Black or African American	11 (3.7)	9 (3.1)		
	Asian	20 (6.8)	22 (7.5)		
	Other	10 (3.4)	14 (4.8)		
**Ethnicity, n (%)**					.34
	Hispanic	16 (5.3)	25 (8.3)		
	Non-Hispanic	277 (92.3)	270 (89.1)		
	No answer	7 (2.3)	8 (2.6)		
**BMI classification (intervention: n=297; control: n=291), n (%)**					.56
	Underweight	3 (1.0)	2 (0.7)		
	Normal	65 (21.9)	78 (26.8)		
	Overweight	100 (33.7)	91 (31.3)		
	Obese	129 (43.4)	120 (41.2)		
**Biometric measurements, mean (SD)**					
	Weight (lb; intervention: n=297; control: n=292)	185.5 (46.9)	178.4 (43.7)	.06	
	Height (in; intervention: n=297; control: n=291)	65.5 (3.5)	65.2 (3.3)	.26	
	BMI (kg/m^2^; intervention: n=297; control: n=291)	30.4 (7.1)	29.5 (6.7)	.12	
	Waist circumference (in; intervention: n=294; control: n=289)	37.6 (6.5)	36.4 (6.0)	.02	
	Systolic BP^a^ (mm Hg; intervention: n=297; control: n=291)	121.0 (9.6)	119.2 (10.2)	.03	
	Diastolic BP (mm Hg; intervention: n=297; control: n=291)	75.2 (8.0)	74.3 (7.9)	.17	
	HbA_1c_^b^ (%; intervention: n=297; control: n=292)	5.2 (0.6)	5.2 (0.5)	.47	
	Total cholesterol (mmol/L; intervention: n=296; control: n=291)	190.6 (38.7)	196.8 (38.0)	.05	
	HDL-C^c^ (mmol/L; intervention: n=296; control: n=292)	58.0 (14.5)	59.3 (14.7)	.29	
	LDL-C^d^ (mmol/L; intervention: n=296; control: n=292)	118.7 (34.5)	123.5 (34.6)	.10	
	TC/HDL ratio^e^ (intervention: n=296; control: n=292)	3.5 (1.0)	3.5 (1.2)	.57	

^a^BP: blood pressure.

^b^HBA_1c_: hemoglobin A_1c_.

^c^HDL-C: high-density lipoprotein cholesterol.

^d^LDL-C: low-density lipoprotein cholesterol.

^e^TC/HDL ratio: total cholesterol/high-density lipoprotein cholesterol ratio.

### Intervention Engagement and Participant Retention

To approximate real-world scenarios, this study did not have a specific plan to promote participant engagement with the intervention or retention of participants in the study beyond ensuring that their Fitbit device was synced with the mobile app and initial communication with their personal health coach occurred. The median wear time for Fitbit was observed to be 325 (IQR 154-372) days, and 264 (88%) participants used health coaching at least once. Of the 603 participants who completed entrance screening and thus were included in the study, 8 (1.3%) withdrew, 519 (86.1%; intervention: n=251; control: n=268) completed exit surveys, and 469 (77.8%; intervention: n=227; control: n=243) completed exit biometric screening (Figure 4).

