### Study Setting and Participants

This study was conducted in Worcester, Massachusetts, with employees of UMass Memorial Health (UMMH). To be eligible, participants must have been enrolled on a UMMH-sponsored health plan, had to own a smartphone, had to be 18 years of age or older, and agreed to consent to the study (Figure 1). Participants who were pregnant at the time of enrollment, did not speak English, or were incarcerated were excluded from the study. The study had an a priori enrollment goal of up to 700 employees, which represents roughly 7.5% of the entire eligible population. The sample size for this study was derived based on the pragmatics of resource availability. All eligible employees were invited to participate in the study through electronic communication and a home mailer. To be enrolled in the study, participants had to electronically sign informed consent, fill out a baseline survey and demographics, use a self-scheduling service to pick an appointment for their initial biometric screening, and then complete said screening in person. Participants were then randomized to either the intervention arm or the control arm. Randomization was conducted using a random number generator to provide a random number of 1 or 2 for each of the study participants. A permuted block design with random block sizes was used to generate the randomization sequence. That sequence was loaded into a randomization module using a free, secure, and robust data collection platform called REDCap (Research Electronic Data Capture; developed at Vanderbilt University) so that it was readily available during the in-person screening process. Participants were asked to schedule an exit biometric screening at the end of the 12-month study period. Because this intervention being investigated is designed to help users improve their health behaviors in alignment with the advice of their health care providers and not to make medical decisions, the risk of harm to health is low. Participants were free to withdraw from the study at any time.

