### Statistical Analysis

In this paper, we present descriptive statistics for baseline characteristics and overall engagement among the participants assigned to the intervention group using proportions and the mean for the distribution of categorical and continuous variables, respectively. The study will evaluate its primary objectives using intention-to-treat analysis. A 2-tailed Student *t* test for independent samples will be used to compare the mean of continuous variables, and a chi-square or Fisher exact test will be used to compare categorical variables between the intervention and control groups. Secondary objectives will be evaluated using group-based trajectory modeling to identify distinct trajectories of engagement and adherence, the association of distinct trajectories with baseline behavior and comorbidities, and performing an intervention-only analysis where the treatment effect of the intervention is evaluated across different trajectories of engagement. Additional exploratory analyses will consider accounting for possible contamination based on the self-reported use of wearable health and fitness devices among the control group participants. There are no plans to use biological specimens in ancillary studies. Data collection questionnaires can be provided upon request.

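### All 603 participants are said to have completed entrance biometric screening before allocation, but Table 2 has baseline values for only 583 to 589, with an unexplained gap that is larger in the control arm

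*Protocol article*

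**What the plan says.** The protocol article, under Study Setting and Participants, makes the in-person biometric screening a step of enrolment that precedes allocation: participants had to schedule it "and then complete said screening in person. Participants were then randomized to either the intervention arm or the control arm". Intervention Engagement and Participant Retention repeats that the screening was finished by all: "Of the 603 participants who completed entrance screening and thus were included in the study".

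Other places are looser. Baseline Characteristics speaks of attendance: "603 individuals attending the biometric screening and getting randomized to the intervention (n=300, 49.8%) or control group (n=303, 50.2". Study Setting and Participants says that the randomisation sequence was loaded into REDCap "so that it was readily available during the in-person screening process". Data Collection and Management and Table 1 put allocation and screening at the same visit.

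Table 2 prints a denominator for each biometric row, for example "Diastolic BP (mm Hg; intervention: n=297; control: n=291" and "Waist circumference (in; intervention: n=294; control: n=289". None reaches 300 or 303.

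On the analysis, the abstract defines the primary outcomes as changes, cardiometabolic biomarkers among them. Statistical Analysis names a two-sample t test for continuous variables and says: "The study will evaluate its primary objectives using intention-to-treat analysis".

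**The concern.** If screening was completed by everyone before allocation, each randomised participant should have a baseline record, apart from single items that failed. Missing values should also be unrelated to arm, except by chance. Table 2 shows a shortfall on every row, always larger in control, and the text does not account for it. Either *completed* means something less than it says, or some records did not reach the analysis dataset, or the sequence at the visit was not always as described. A reader cannot tell which.

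The biomarkers are primary outcomes defined as change, so the baseline is half of each outcome. A participant without it cannot enter a t test on change, and the analysed set is then smaller than the randomised set that the intention-to-treat statement refers to.

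**Working it through.** **Step 1. The stated figure.** 300 + 303 = 603, so the number randomised reproduces.

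**Step 2. Baseline values present.** Inputs are the Table 2 denominators. Missing = 300 or 303 minus the row n.

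| Measure | n, intervention / control | Total | Missing, intervention | Missing, control | Fisher P |
|---|---|---|---|---|---|
| BMI, height, systolic and diastolic BP | 297 / 291 | 588 | 3 (1.0%) | 12 (4.0%) | .033 |
| Weight, HbA1c | 297 / 292 | 589 | 3 (1.0%) | 11 (3.6%) | .055 |
| Total cholesterol | 296 / 291 | 587 | 4 (1.3%) | 12 (4.0%) | .073 |
| HDL-C, LDL-C, ratio | 296 / 292 | 588 | 4 (1.3%) | 11 (3.6%) | .114 |
| Waist | 294 / 289 | 583 | 6 (2.0%) | 14 (4.6%) | .109 |

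The rows share participants, so they are not independent pieces of evidence.

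**Step 3. Are the smaller denominators misprints?** No. The BMI categories sum to 3 + 65 + 100 + 129 = 297 and 2 + 78 + 91 + 120 = 291. The text gives 440 overweight or obese as 74.8%. 440/588 = 74.8%, whereas 440/603 = 73.0%.

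**Step 4. Who can enter a t test on change in BMI or BP?** Exit screening is reported for 227 intervention and 243 control participants, so 300 − 227 = 73 and 303 − 243 = 60 are lost at exit. The overlap of missing baseline with missing exit is not given, so the total loss has bounds:

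- Intervention: 73 to 73 + 3 = 76, or 24.3% to 25.3%.
- Control: 60 to 60 + 12 = 72, or 19.8% to 23.8%.

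The loss is larger in the intervention arm at every possible overlap, by 24.3 − 23.8, about 0.6 points (unrounded), to 25.3 − 19.8 = 5.5 points. From exit loss alone the difference is 24.3 − 19.8 = 4.5 points. If baseline and exit missingness are independent (assumption), the pairs number 227 × 297/300 = 224.7 and 243 × 291/303 = 233.4. The losses are then 25.1% and 23.0%, a difference of 2.1 points, so the baseline gap narrows the imbalance. It could widen it, by at most 1 point, only if at least 9 of the 12 controls without a baseline also missed the exit visit.

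The arm counts sum to 470, while the text gives 469. Removing one participant from either arm leaves the direction in percentage terms unchanged.

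**Step 5. Direct bias from the missing baselines.** If those missing differ by d from the rest, each arm mean shifts by d times its missing fraction. With d = 0.5 SD (assumption), the contrast shifts by 0.5 × (12/303 − 3/300) = 0.015 SD if the shifts have the same sign, and by 0.5 × (12/303 + 3/300) = 0.025 SD if they are opposite. For comparison, the difference detectable with 227 and 243 participants at 80% power and two-sided 5% is (1.960 + 0.842) × √(1/227 + 1/243) = 0.259 SD.

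**The case against.** Completing a screening visit is not the same as having every value in the dataset. Items may go unrecorded and samples may fail, and the denominators do vary a little by item. Ethical Considerations says that the screening data were held by the outside laboratory and transferred electronically, so unlinked records are another ordinary explanation. All of these fit screening first and allocation second. Table 2 prints its denominators openly, and the participant flow diagram (Figure 4), which could not be seen in the text reviewed, may bear on the gap. All of this stands, and it limits the point to a mismatch that needs an explanation.

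Two stronger readings are tempting. The first is that some baselines were taken, or skipped, after allocation was known. Allocation at the same visit and a sequence at hand in REDCap make that possible, but no passage says it happened. A gap of 3 against 12 can arise by chance, and only the BMI, height and BP rows fall below P=.05. The second is that the change analysis loses more controls than intervention participants. That is true of the baseline part alone. Once exit loss is counted, the direction reverses.

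It can also be said that the handling of missing data belongs in an analysis plan that is not shown. That is fair, and no omission is alleged. The point about the model concerns the test that the article does name.

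**Conclusion.** The mismatch is real. Two sections say that all 603 completed screening before allocation, while 14 to 20 of them lack a given baseline biometric, more often in control, and the text does not explain it. The documents do not establish that the order of events was wrong.

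The consequence for the analysis is modest. It concerns biomarker change only, not the survey or claims outcomes. For BMI and BP, between 224 + 231 = 455 and 227 + 243 = 470 of 603 participants can enter a t test on change, and most of the shortfall comes from exit loss rather than from missing baselines. The net loss is larger in the intervention arm. Direct bias from the missing baselines is about 0.015 to 0.025 SD under the assumed 0.5 SD difference, at most a tenth of the 0.259 SD detectable difference. These figures rest on the printed arm counts at exit and on bounds for an overlap that is not reported.

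**What to change.** 1. Reconcile *completed* (Study Setting and Participants; Intervention Engagement and Participant Retention) with *attending* (Baseline Characteristics) and with Table 2. State, by arm, how many participants had each baseline measure before allocation and why the rest are missing. The REDCap allocation records and the laboratory's screening records should settle this. Cost: a data query and corrected wording.

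2. Analyse each biomarker with a constrained longitudinal model in place of the t test on change: baseline and 12-month values both as outcomes, with a common baseline mean across arms. Participants with either value then contribute (at least 297 + 291 = 588 for BMI and BP), and baseline is adjusted for. The gain has limits: at most 3 intervention and 12 control participants bring in an exit value that the t test would discard, and those with only a baseline add little direct information on the treatment effect. Cost: one standard mixed model in SAS, no new data, and a missing-at-random assumption that should be stated.

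3. Only if the record check finds baselines taken after allocation, add a sensitivity analysis that sets those values to missing.

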**Figure 4 figure4:**
[figure not shown]
UMass Fitbit Care Study participant flow: flow of participants through the UMass Fitbit Care study, showcased by the CONSORT (Consolidated Standards of Reporting Trials) diagram. UMMHC: UMass Memorial Health Center.

## Discussion

### Overview

We describe the design, rationale, and baseline characteristics of a randomized control trial of a multimodal DBCI from Fitbit on improving lifestyle behaviors and cardiometabolic health in a general, rather than disease-specific, population. The high retention rate and balanced distribution of baseline characteristics, paired with a comprehensive assessment of the intervention’s impact on behavioral, cardiometabolic biomarkers, and medical expenditure, will allow for detailed evaluation of the intervention for primary and secondary endpoints.

### Comparison With Prior Work

Research on the effectiveness of DBCIs for chronic disease prevention has yielded mixed results with regard to behavioral change and cardiometabolic outcomes. One randomized controlled trial led by Toro-Ramos et al [34] assessed the effectiveness of a lifestyle app in individuals with prediabetes, in which significant weight loss was observed in the intervention group, but there was no significant difference in hemoglobin A_1c_ levels between the intervention and control groups at 1 year (mean difference 0.006%; n=103; *P*=.93) [35]. Likewise, another study investigating a mobile diabetes prevention program found a 1.9% (n=163) decrease in hemoglobin A_1c_ among intervention participants compared to the control group, but there were no improvements in patient-reported behaviors such as mood after 12 months [36]. Additionally, such interventions have often focused on evaluating behaviors within disease-specific populations [34,37-40].

### Future Aims

Therefore, we aim to adopt a more holistic approach to behavior change intervention research by evaluating the effectiveness of a DBCI intervention in a broader, real-world population and assessing changes in behavior across 4 key areas: physical activity, nutrition, sleep, and mindfulness. Additionally, we will conduct comprehensive biometric evaluations using both digital and laboratory biomarkers, which will contribute valuable insights to the existing literature.

There are several potential mechanisms through which Fitbit DBCI can affect healthy behavior changes, which lie upstream of factors that impact the onset and progression of chronic diseases. The Lifestyle Medicine Research Summit proposed that promotion of healthy lifestyle behavior can interrupt the pathogenesis of chronic diseases and possibly reverse it [41-44]. The Health Belief Model is a well-established theory to explain an individual’s decision-making for a behavioral change [45]. We propose that an integration of these 2 frameworks, as described in Figure 5 [43], can provide theoretical underpinning for the impact of the Fitbit DBCI on chronic diseases. Fitbit DBCI’s ability to pair tracking of behavior with nudges and coaching that can be delivered through telecommunications and motivational messaging can act on lifestyle behaviors that lie upstream of factors that lead to chronic diseases [37,46-50]. Support for individual goal setting and self-monitoring through alerts based on certain patterns of inactivity or pushing motivational messages based on the accomplishment of healthy behaviors can motivate individuals, promote self-efficacy, and provide cues for action [51-53]. It offers a holistic approach to improving lifestyle behaviors and is responsive to the USPSTF’s recommendation for tailoring behavioral intervention to individuals’ needs.

In our study, we observed a high adherence to wearable devices, with a median wear time of 325 (IQR 154-372) days. We had an 86.1% (n=519) retention rate for exit surveys that evaluated self-reported behavioral outcomes and a 77.9% (n=490) retention rate for exit visits that measured cardiometabolic biomarkers. Our results are consistent with findings from prior research on DBCIs for diabetes and hypertension prevention [26,39].

Further secondary analysis of the data from this study can inform the feasibility and acceptance of providing multimodal DBCIs for employees in a workplace setting. Additionally, through the collection of data over the course of the year from the Fitbit intervention, we will be able to perform secondary data analysis that characterizes the intensity of the coaching intervention, which is likely to be a key determinant of its efficacy. A 3-year study showed that individualized biweekly counseling decreased sedentary time and promoted healthy behavior [41,42]. However, it is unlikely that all users of the program require an intervention of this intensity. We will be able to perform analysis to understand factors associated with goal setting and the self-efficacy of participants for affecting behavioral change as measured through standardized questionnaires. Thus, our findings will inform optimal intervention practices for implementing DBCI programs at scale, where participant-reported outcomes can be used to facilitate tailored behavioral counseling for participants and align DBCI programs with USPSTF recommendations for individualizing interventions.

**Figure 5 figure5:**
[figure not shown]
Conceptual framework of Fitbit’s multimodal digital behavior change intervention (DBCI) for improving healthy behaviors and cardiometabolic outcomes. Components of Fitbit’s DBCI are depicted in blue boxes. The framework represents a combination of the Health Belief Model and the framework proposed by Bodai et al.

### Strengths and Limitations

Several aspects of the study represent methodological strengths, which include the use of a randomized design, rigorous and standardized outcome evaluation, and robust adherence to the protocol. However, the study’s limitations should also be noted when interpreting the results from this study. Our study lacks an active control and therefore we cannot estimate treatment effects of activity tracking and DBCI separately. However, the intended use of Fitbit health coaching is as a combination, and therefore, this study estimates the combined treatment effect of this multimodal intervention. Our study sample underrepresents Black or African American, Hispanic, and Asian staff, suggesting a need for future studies to implement robust recruitment strategies to target underrepresented groups. Moreover, our study sample was selected from employees at an urban academic medical center, which may suggest that these participants are already engaging in healthy behaviors given their health backgrounds. Our study sample included individuals who volunteered to participate in digital health research. Our baseline characteristics suggest that there is skewness in demographic representation such that individuals more likely to participate in these studies are enrolled in this study, which may account for our high adherence and retention rates. While that limits the generalizability of the study findings, the randomized assignment of interventions balances any possible bias that may emerge from early responders to the invitation. Lifestyle behavior was measured using standardized surveys with high face validity, but these were not validated instruments, such as the Pittsburgh Sleep Quality Index, 24-hour food recall, perceived stress scale, etc, which limits the external generalizability of the findings; however, differences between groups in these measures are unlikely to be affected by them.

### Conclusions

To our knowledge, this is one of the largest evaluations of a multimodal DCBI’s impact on physical activity, nutrition, sleep, and mindfulness among participants who were recruited independent of their underlying disease status. It is also among the only studies that comprehensively evaluates the impact of the DBCI on the sequelae of healthy behavior by measuring cardiometabolic biomarkers and abstracting medical expenditure data. Finally, data from this study can help understand adherence to DBCIs over the period of 1 year and elucidate the association between intensity of coaching, self-reported motivation for changing behavior, and objective measurement of health behavior trajectories from wearable health and fitness devices and wirelessly connected scales. Taken together, the findings from this study have the promise to provide useful insights for individualizing the Fitbit intervention among otherwise healthy people, as recommended by the 2022 USPSTF.

